### Sample

2.6

Seven post-primary schools in NI will be recruited to the feasibility trial. Eligible schools will include those that currently have a Year 11 group (i.e. adolescents aged 14–16 years). There are 216 such schools in NI in 2012/13. Schools will be excluded if they are defined as hospital, independent or Irish language schools or have less than 30 pupils in Year 11. The study sample will also be stratified to reflect the main categories of schools. In NI schools are categorised as ‘secondary’ and ‘grammar’ with the latter using academic ability to select pupils. Various management structures exist with ‘controlled’ schools managed by one of five education and library boards and ‘voluntary’ schools managed by a board of trustees (usually local churches). The Catholic Church manages a significant number of voluntary (‘maintained’) schools. Although religion is not a criterion for attendance, most pupils at controlled schools are from Protestant denominations and most of those attending maintained schools are Catholic. There are also a number of ‘integrated’ schools, which aim to provide a religiously mixed environment. In order to capture diversity and reflecting the organisation of education in the special circumstances of NI, recruited schools will consist of the following: 1 controlled integrated; 1 controlled grammar; 2 voluntary Catholic grammar; 2 secondary schools in deprived areas; and 1 voluntary ‘other’ management.

Potentially eligible schools will be identified from those attending RSE teacher training (as provided by the Public Health Agency of NI). This training session will introduce the intervention and provide an overview of the research. RSE teachers in attendance will be asked to indicate if they are interested in receiving more information about the research. The schools that we will approach in the first instance will be selected on the basis of 1) their expressed interest and 2) their fit with our recruitment criteria. Schools which decline to participate will be replaced by the next listed school from the list of all eligible schools stratified by school management type and deprivation.

The target population is adolescents aged 14–16 in Year 11. The total sample size of seven schools is likely to provide access to approximately 630 pupils. This is based on the average size of year 11 groups in schools in 2011/12 (mean = 114; median = 113) (DOE, 2012) and allows for an 80% consent rate (Henderson et al., 2007).

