### Randomisation procedures

2.7

Schools will be the unit of randomisation, with four randomly allocated to the intervention group and three to the control group. After baseline data collection, the two sets of pairs (Catholic grammar and deprived secondary) will be randomised as pairs to ensure that one of each type is in the intervention arm. Simple random selection will be used for the remaining three schools to allocate two to the intervention group and one to the control group.

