### Data analysis

2.9

Primary analyses will be on an intention-to-treat basis, using all participants in the groups they were randomised to, regardless of the intervention received.

*Participant flow and recruitment*: Summary statistics on consent, withdrawal and dropout will be collated for both trial groups. For each group, the numbers of clusters and participants randomly assigned, receiving intended intervention, completing the study protocol, and analysed for the outcomes will be presented in a CONSORT flow diagram (Schulz, Altman, & Moher, 2010).

*Baseline data*: Appropriate descriptive summaries of baseline demographic and questionnaire data for pupils and parents from the two study arms will be tabulated. Descriptive summaries will be produced for baseline data at cluster level where appropriate.

*Pupil outcomes (5 and 9 month follow-up):* Questionnaire data from pupils will be analysed using frequencies and descriptive statistics. Differences between the trial groups and broad indicators of effect size will be reported. As this is a feasibility study, it is not powered to detect significant differences and inferential analyses will not be performed. Descriptive statistics will be used to report the proportion (categorical outcomes) or mean scores (continuous outcomes) for the intervention and control groups. Reliability of psychometric instruments will be analysed through recourse to classical reliability theory involving factor analysis and calculation of Cronbach's alpha.

*Effect size estimates:* As noted, this feasibility study will measure surrogate outcomes associated with reductions in unintended pregnancy such as abstinence from sex or avoidance of unprotected sex (categorical variables). Effect sizes will be calculated from the differences in proportions between the intervention and control groups. A number of secondary outcomes are also being investigated (continuous variables). Effect sizes will be calculated from the differences in the mean scores between the intervention and control groups taking into account the standard deviation.

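### Effect sizes are plain arm differences although the pairs are allocated 1:1 and the other three schools 2:1, so they can be biased by school type with no intervention effect

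*Protocol article*

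**What the plan says.** Section 2.6 (Sample) sets the seven schools by type: "1 controlled integrated; 1 controlled grammar; 2 voluntary Catholic grammar; 2 secondary schools in deprived areas; and 1 voluntary ‘other’ management". It also explains that types differ in intake: "In NI schools are categorised as ‘secondary’ and ‘grammar’ with the latter using academic ability to select pupils".

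Section 2.7 (Randomisation procedures) fixes the arm sizes: "Schools will be the unit of randomisation, with four randomly allocated to the intervention group and three to the control group". The two pairs "will be randomised as pairs to ensure that one of each type is in the intervention arm". For the rest: "Simple random selection will be used for the remaining three schools to allocate two to the intervention group and one to the control group".

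Section 2.9 (Data analysis) then defines the effect measures. For abstinence or avoidance of unprotected sex: "Effect sizes will be calculated from the differences in proportions between the intervention and control groups". For the continuous secondary outcomes: "Effect sizes will be calculated from the differences in the mean scores between the intervention and control groups taking into account the standard deviation". Neither definition mentions the pairs, the trio, weighting or baseline values. The same section states that the results are descriptive and that no inferential analysis will be done.

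**The concern.** The chance of receiving the intervention is 1/2 for a school in either pair and 2/3 for one of the other three. When allocation ratios differ between strata and the analysis ignores the strata, the two arms do not have the same expected mix of schools. The crude difference then carries part of any outcome gap between school types, even if the intervention does nothing.

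This is built into the design and is not a chance imbalance that might or might not occur. Section 2.7 pairs two school types in order to balance them across arms, and the estimator in section 2.9 does not use that feature. What is at stake is the set of effect sizes that section 2.4 describes as broad estimates. A bias affects a descriptive point estimate just as it would a tested one.

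**Working it through.** **Inputs from the article.** Seven schools, four intervention and three control; two pairs at 1:1; a trio (controlled integrated, controlled grammar, voluntary other) at 2:1 (sections 2.6 and 2.7). About 630 pupils (section 2.6).

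**The article's own figure.** 7 × 114 × 0.80 = 638 using the mean year-group size, and 7 × 113 × 0.80 = 633 using the median. Both agree with about 630, or 630/7 = 90 pupils per school.

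**Composition of the arms.** There are 2 × 2 × 3 = 12 possible allocations, and all have the same mix:

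| School type | Intervention (4 schools) | Control (3 schools) |
|---|---|---|
| Catholic grammar | 1/4 = 25% | 1/3 = 33% |
| Deprived secondary | 1/4 = 25% | 1/3 = 33% |
| Trio | 2/4 = 50% | 1/3 = 33% |

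**Expected difference with no effect, schools of equal size.** Let P1 and P2 be the means of the two pairs, P = (P1 + P2)/2, and U the trio mean.

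- Expected intervention mean = (P1 + P2 + 2U)/4 = P/2 + U/2.
- Expected control mean = (P1 + P2 + U)/3 = 2P/3 + U/3.
- Expected difference = (U − P)/6.

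**Size.** The article gives no outcomes by school type, so the gap U − P is assumed:

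| Assumed gap (points) | 0 | 5 | 10 | 15 | 20 | 30 |
|---|---|---|---|---|---|---|
| Expected crude difference | 0 | 0.8 | 1.7 | 2.5 | 3.3 | 5.0 |

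For a continuous outcome, a gap of 0.5 SD gives 0.5/6 = 0.08 SD. With assumed school sizes from 60 to 120 pupils and a 10-point gap, the average over the 12 allocations is again about 1.7 points.

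**Illustration with assumed school values and no effect.** Pairs at 72/78 and 90/94, trio at 85/90/95. Then P = 83.5, U = 90, and (90 − 83.5)/6 = +1.08. Over the 12 allocations:

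- Crude difference: mean +1.08, SD 3.18, range −4.75 to +6.92. Root mean square error √(3.18² + 1.08²) = 3.36.
- Stratified difference, strata weighted equally: mean 0, SD 3.15.
- Stratified difference, weights n1·n0/(n1+n0) schools, that is 1/2, 1/2 and 2/3: mean 0, SD 3.27, range −6.0 to +6.0.

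Stratifying removes the expected bias. It barely changes the spread.

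**Sign.** Keep the pairs as they are and set the trio at 75/80/85, so U = 80. The expected crude difference is (80 − 83.5)/6 = −0.58.

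**Scale against sampling error.** With assumed prevalence p = 80%, 90 pupils per school and intracluster correlation (ICC) 0.01 to 0.05, the standard error of the crude difference is √{[ICC·p(1−p) + (1−ICC)·p(1−p)/90] × (1/4 + 1/3)} = 4.4 to 7.5 points.

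**The case against.** The case for leaving the plan alone is substantial. The key outcomes are implementation quality, recruitment and retention. The effect sizes are labelled broad, no test is done on them, and nothing in the article says they will set the target difference of the phase III trial. The bias is one sixth of a gap nobody has measured, set against a standard error of several points. In the illustration, stratifying cuts total error only from 3.36 to between 3.15 and 3.27. With the trio at 75/80/85, the crude error is √(3.18² + 0.58²) = 3.23, slightly below the 3.27 of the size-weighted stratified estimate. All of this stands, and it limits the weight of the point.

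Three stronger readings are tempting, and the article does not support them.

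- A reader might infer that the crude difference is necessarily biased. It is not: Catholic grammars at 90%, deprived secondaries at 70% and a trio at 80% give exactly zero.
- A reader might infer that poorer outcomes in deprived schools make the bias favour the intervention. Catholic grammars are over-represented in control by the same amount, so the sign depends on the trio against all four paired schools. The −0.58 example keeps the deprived schools lowest.
- A reader might fault the plan because each unpaired school type appears in only one arm. That follows from recruiting one school of each such type, and no reanalysis cures it.

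A separate analysis plan might add stratification. The article, however, does not leave the estimator open: it states a plain arm-level contrast.

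**Conclusion.** The point holds as a modest, removable design bias in a stated estimator. School-type mix differs between arms in all 12 allocations. With equal school sizes and no effect, the expected crude difference is one sixth of the gap between the trio mean and the mean of the four paired schools. That is 0.8 to 2.5 points if the gap is 5 to 15 points. The composition and the formula follow from sections 2.6, 2.7 and 2.9. The gap is an assumption, so neither size nor direction can be stated for this trial.

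The bias is probably small beside the chance variation of seven schools, and no trial decision rests on it. It is worth correcting because the strata already exist, the correction is descriptive, and the crude figure would otherwise be reported without a warning about its mix of schools.

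**What to change.** In section 2.9:

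1. Define the effect size as the within-stratum difference: the two within-pair differences and the trio's intervention-minus-control difference, combined with weights stated in advance. Equal weights and n1·n0/(n1+n0) weights both have zero expectation under no effect.
2. Show the crude arm difference beside it, labelled as not balanced by school type.
3. List the seven school-level values, so that readers can see how far single schools drive the result.
4. Optionally, because section 2.7 places randomisation after baseline data collection, give a change-from-baseline or baseline-adjusted version as a secondary description.

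The cost is a few sentences and a short table, with no new data, test or change to randomisation. The trio contrast will still compare different school types. The text should therefore say that stratifying removes the expected bias and leaves the chance spread.

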### Control group

2.3

Pupils in the control group of the study will not receive the *If I Were Jack* intervention and will continue with normal RSE practice. We will determine resistance to assignment to the control group by recording refusal to participate or difficulties with retention at follow-up. If we experience difficulties in this regard, we will consider alternative designs for the main trial.

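### Effect sizes are stated as plain arm differences, although two school pairs are randomised 1:1 and the other three schools 2:1, so the arms differ in school mix by design

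*Protocol article*

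**What the plan says.** Section 2.6 (Sample) recruits seven schools of set types: "1 controlled integrated; 1 controlled grammar; 2 voluntary Catholic grammar; 2 secondary schools in deprived areas; and 1 voluntary" school under other management.

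Section 2.7 (Randomisation procedures) makes the school the unit of randomisation, "with four randomly allocated to the intervention group and three to the control group". Within that total, "the two sets of pairs (Catholic grammar and deprived secondary) will be randomised as pairs", so that each pair supplies one school to each arm. For the rest, "Simple random selection will be used for the remaining three schools to allocate two to the intervention group and one to the control group".

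Section 2.9 (Data analysis) defines the effect measure. For the categorical behaviour outcomes, "Effect sizes will be calculated from the differences in proportions between the intervention and control groups". For the continuous secondary outcomes, "Effect sizes will be calculated from the differences in the mean scores between the intervention and control groups taking into account the standard deviation". Neither sentence mentions pairs, school type, strata or weights. Cluster-level summaries are mentioned for baseline data only. The section describes the results as broad, descriptive indicators without inferential analysis.

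For consent, withdrawal and dropout, section 2.9 only tabulates summaries for each arm. Section 2.3 (Control group) separately says that resistance to being a control will be judged by "recording refusal to participate or difficulties with retention at follow-up".

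**The concern.** The randomisation has three strata, and the chance of receiving the intervention is not the same in all of them. When that happens, a comparison of whole arms mixes the intervention effect with differences between strata. This is not chance imbalance that might go either way on the day. It is the same in every allocation the procedure can produce.

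The school types were chosen to capture diversity, so the authors themselves expect them to differ. The trial is meant to supply broad estimates of effect size for the outcomes of a later phase III trial. Because no intervals or tests are planned, the point estimate is what readers will carry forward. A descriptive figure that is not centred on zero under no effect is a poor thing to carry forward when the cure is a small change in how it is computed.

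**Working it through.** **Inputs from the article.** Seven schools; two Catholic grammar, two deprived secondary and three single schools of different types (2.6); each pair split 1:1 and the set of three split 2:1 (2.7); effect sizes as arm differences in proportions or means (2.9).

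**The article's own figures.** The 4:3 split follows from the strata: 1 + 1 + 2 = 4 intervention and 1 + 1 + 1 = 3 control. The expected total of about 630 pupils is also consistent with its inputs: 7 × 114 × 0.8 = 638.4 using the mean year size, and 7 × 113 × 0.8 = 632.8 using the median.

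**Allocation probabilities.** There are 2 × 2 × 3 = 12 equally likely allocations. Each of the four paired schools is in the intervention arm in 1/2 of them, and each of the three single schools in 2/3.

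**School mix, identical in all 12 allocations.**

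| Arm | Catholic grammar | Deprived secondary | Set of three |
|---|---|---|---|
| Intervention (4 schools) | 1/4 | 1/4 | 1/2 |
| Control (3 schools) | 1/3 | 1/3 | 1/3 |

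The set of three is over-represented in the intervention arm by 1/2 − 1/3 = 1/6.

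**Null expectation of the arm difference.** Let C, D and S be the mean outcome in Catholic grammar schools, deprived secondaries and the set of three. Assume equal school sizes and no intervention effect:

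(C + D + 2S)/4 − (C + D + S)/3 = (2S − C − D)/12 = [S − (C + D)/2]/6

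**Size.** The article gives no outcome levels by school type, so the gap S − (C + D)/2 is an assumption.

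| Assumed gap (percentage points) | Bias = gap/6 |
|---|---|
| 5 | 0.8 |
| 10 | 1.7 |
| 20 | 3.3 |
| 30 | 5.0 |

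The sign follows the sign of the gap. Three illustrations, all with assumed rates:

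- C = 10%, D = 35%, S = 15%: (15 − 22.5)/6 = −1.25 points.
- C = 5%, D = 30%, S = 20%: (20 − 17.5)/6 = +0.4 points.
- C = 85%, D = 55%, S = 70%: (70 − 70)/6 = 0.

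**Stratified difference.** Taking the arm difference inside each stratum and combining with fixed weights gives a null expectation of 0 in every scenario enumerated.

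**Cost in precision if schools vary independently and type does not matter.** In units of the between-school variance, the crude factor is 1/4 + 1/3 = 0.583. Within a pair the difference has variance 1 + 1 = 2; within the set of three it has 1/2 + 1 = 1.5.

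- Weights 2/7, 2/7, 3/7: 2 × (2/7)² × 2 + (3/7)² × 1.5 = 0.602, so the standard error ratio is √(0.602/0.583) = 1.016.
- Weights 0.3, 0.3, 0.4: 2 × 0.09 × 2 + 0.16 × 1.5 = 0.600, ratio 1.014.

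**What weighting cannot do.** Suppose the outcome is 85% in both Catholic grammars, 60% in both deprived secondaries, and 65%, 85% and 75% in the three single schools. The crude bias is (75 − 72.5)/6 = 0.4 points, while the spread over the 12 allocations has an SD of 4.8 points. The stratified difference has no bias but an SD of 5.2 points (5.25) with weights 2/7, 2/7, 3/7. The single-school stratum difference takes the values +15, −15 and 0, SD 12.2, so a weight of 0.4 gives 0.4 × 12.2 = 4.9 points. That spread remains because each single type sits wholly in one arm.

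**The case against.** **The comparison is only descriptive, and seven schools are noisy.** Between-school SDs of 5 and 10 points would give standard errors of the crude difference of about 3.8 and 7.6 points, larger than most of the plausible biases. No decision rule in the article hangs on the effect size. This stands as a limit on importance. It does not make a biased figure preferable to an unbiased one that costs almost nothing.

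**The article does not say crude or pooled, and a fuller analysis plan may specify weighting.** True, and such a plan may settle the matter. But the article does state an estimator, the difference between the two groups, and as stated it does not match the randomisation described two sections before.

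**Stronger readings that the article does not support.**

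- A reader might infer that the comparison favours the intervention whenever deprived secondaries have more risk behaviour. The sign depends on the average of both pair types against the set of three. In the second illustration above, deprived schools have the highest risk and the bias still goes against the intervention.
- A reader might infer that retention is compared as a crude arm difference and drives redesign of the main trial. Section 2.9 defines no retention contrast. Section 2.3 concerns resistance among controls, sets no threshold, and says only that alternative designs would be considered.
- A reader might expect a large gain in precision from stratifying. Such gains appear mainly when school sizes are assumed to be very unequal and the three single schools are given one common mean. Section 2.6 makes them three different types.
- A reader might think that stratifying removes all confounding of school type with arm. Within the set of three it cannot.

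**Conclusion.** The point holds in a limited form. The 1/2 and 2/3 allocation probabilities and the fixed difference in school mix are exact and follow from section 2.7 alone. The effect size as worded in section 2.9 is then off centre by one sixth of the stratum gap. On assumed gaps of 5 to 30 points that is 0.8 to 5.0 points, in either direction, and it can be zero. The formula assumes equal school sizes; if pupils are pooled across schools of unequal size, the school weights change and the bias is no longer exactly one sixth of the gap.

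The confounding is partial, since each pair type appears in both arms, and the bias may well be smaller than the chance variation from seven schools. The case for change rests on its low cost and on the fact that the unstratified figure is the one the trial intends to report. For consent, withdrawal and dropout there is no wrongly defined contrast, only a risk that readers set two arm figures with different school mixes side by side.

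**What to change.** In the effect-size sentences of section 2.9:

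- Compute each difference in proportions or means within the three randomisation strata and combine the three with weights stated in advance, for example 2/7, 2/7, 3/7 (proportional to schools) or 0.3, 0.3, 0.4 (inverse variance for independent schools of equal variance).
- Report this as the effect size, with the stratum or school-level results and the crude difference beside it.
- State that each of the three single schools is the only one of its type, so the weighting removes only the bias from the unequal allocation ratio.

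For consent, withdrawal and dropout, add the figures by stratum or school to the arm summaries.

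The change needs no new data: a sentence or two of text and some extra tabulation. If school type is irrelevant, the standard error rises by about 1.4% (weights 0.3, 0.3, 0.4) to 1.6% (weights 2/7, 2/7, 3/7). If the three single schools differ strongly from one another while the paired schools do not, the cost can be greater: in the mixed example above the SD goes from 4.8 to 4.9 points with the first set of weights and to 5.2 with the second.

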### Ethical considerations

2.10

Ethical approval for the study has been granted by the research ethics committee of the School of Nursing & Midwifery, Queen's University Belfast in April 2014 (ref: 04.02.02.V2). We will write to parents to inform them about the research and offer them the opportunity to withdraw their child from the study. The letter will provide the full contact details of the principal investigator, research fellow and chair of the school research ethics committee and will direct parents to a short online information video about the study. Information sheets will be provided to all participants and principals, teachers and pupils will also be given a verbal overview of the research by the research fellow. Written consent will be obtained from principals, teachers, pupils and parents participating in focus groups. Confidentiality will be assured and participants will be made aware that digital recordings will be destroyed following transcription. All information pertaining to individuals and schools will be anonymous from the outset of the study.

